### Criteria for discontinuing or modifying allocated interventions {11b}

Intervention assignment will not be modified during the study. Participants will remain on study unless they themselves withdraw (for both patient and clinicians), in which case the intervention will no longer be available to them.

### Strategies to improve adherence to interventions {11c}

Each intervention can be used as much or as little as desired by the participant following enrollment (for both patients and clinicians). “Dose” of intervention will be assessed via web-based data on page views, time on page, etc., to understand more about the level of use of each intervention by the participants. Participants are provided incentives to join the study and engage in the follow-up assessments.

### Relevant concomitant care permitted or prohibited during the trial {11d}

Usual care for breast cancer patients will be continued throughout the trial. There is nothing prohibited.

### Provisions for post-trial care {30}

Post-trial, all participants will continue to receive usual care for breast cancer patients.

### Outcome measures {12}

#### Primary outcome

The primary outcome of this study is knowledge about the risks and benefits of locoregional treatment measured at the first follow-up assessment. This measure was previously developed and tested by the study team and is defined as the percentage of correct answers (range: 0–100%) from a 5-item scale: higher percentages indicate higher levels of knowledge about treatment risks and benefits [3].

#### Secondary outcomes

We will assess two *key secondary outcomes*, patient-reported cancer worry and breast cancer self-efficacy, both measured at the first follow-up assessment. Cancer worry is measured via the validated eight-item Cancer Worry Scale [19] assessing the degree of cancer-related worry (range: 8 to 40); with higher scores indicating more frequent worries about cancer. Breast cancer self-efficacy is an 11-item validated scale designed to assess breast cancer patients’ overall feelings of control of their cancer and worry about their cancer [20]. It is the composite score obtained from the 11-item validated scale designed to assess breast cancer patients’ overall feelings of control of their cancer and worry about their cancer (range: 11 to 55), with higher scores indicating increased self-efficacy.

There are four *additional secondary outcomes* for this study that each assess additional aspects of PCC. Each are collected at the first follow-up assessment and measured via existing instruments: (1) the six-item Health Care Climate Questionnaire [21, 22], (2) the 12-item Patient Assessment of Cancer Experiences (PACE) [23], (3) the 5-item subjective decision quality (SDQ) measure [24], and (4) three emotional support measures [14].

#### Exploratory outcomes

At 9 months after registration, patients who had invasive cancer at time of enrollment will be surveyed to assess their decision-making and communication regarding systemic treatment. This survey will include a 5-item measure of knowledge about systemic treatment risks and benefits, used in our prior work [3]. At this assessment, the participant will also complete the Cancer Worry Scale a second time, as well as the distress thermometer and the FACT-B Quality of Life scale [25, 26].

#### Clinician measures

We will conduct assessments at time of registration/enrollment, 9 months and 18 months after clinician registration to assess clinicians’ perceptions of their ability to deliver PCC. The two paper surveys include the Patient-Practitioner Orientation scale (PPOS-18 items) [27] and the clinician version of the Health Care Communication Questionnaire (HCCQ) (six items) [21, 22].

### Participant timeline {13}

See Fig. 2 that outlines the stepped wedge time periods and follow-up assessment points.

### Sample size {14}

Sample size depends on the near minimax stepped wedge/parallel hybrid design as described by Girling and Hemming [28]. This design provides close to the maximal possible efficiency across a range of intra-cluster correlations (ICCs) from 0 to 0.2, where larger ICCs are expected for our primary outcome of knowledge as seen from the prior iCanDecide randomized clinical trial (RCT) [3]. Specifically, in our previous iCanDecide trial, we calculated an ICC of 0.15 and a moderate effect size for the iCanDecide decision tool of 0.5 standard deviations. This effect size is equivalent to a little less than one additional question being answered correctly by those who received the intervention.

For SharES, we calculated the sample size required to detect a somewhat smaller standardized effect size of 0.35, which results in only two out of three women getting an additional question correct. Thus, for the planned hybrid stepped wedge design testing the clinic level intervention, we will recruit 25 clinics with a target total sample size of 600 evaluable patients (approximately four patients per clinic per time period) [28–31]. We estimate about 15% will not complete the first follow-up assessment (5 weeks post-surgery), based on our prior iCanDecide trial [3], so we plan to enroll at least 700 participants or around 5 patients per clinic per period. This will allow us to have at least 80% power (alpha=0.05) to detect differences of 0.35 standard deviations between intervention and control subjects for the clinic level intervention (Clinician Dashboard vs. none) and 0.25 standard deviations for the individual-level intervention (ICanDecide-ESE vs. ICanDecide-S) across a wide range of ICCs (0.01 to 0.20). The interaction effect between the two interventions would have to be at least 0.5 standard deviations, or about one additional question correct for each subject, comparable to our effect size in our current intervention, for us to be able to detect it at conventional significance levels.

### Recruitment {15}

Because of the three types of participants in SharES (clinics, clinicians and patients), different recruitment methods are needed for each type. Each is described below.

Surgical clinics

SharES is a CCDR study and is only available to NCORP-affiliated surgical clinics.

Interested clinics will be recruited via Alliance-sponsored webinars and presentations at Alliance meetings. Interested practices must have at least one breast surgeon who is willing to participate, meaning they must agree to consent, review the Clinician Dashboard during the assigned intervention period, and complete surveys. In addition, interested clinics must agree to be randomized to the Clinician Dashboard intervention in the hybrid stepped wedge design (see Fig. 2). The study team will deploy a site screening survey in order to compile a list of interested surgical practices, including questions around practice type, new breast cancer patient volume, engagement of site clinicians, geographic diversity, and ability to enroll patients from minority and/or Spanish speaking patient populations, and history of performance on other NCORP CCDR trials. As sites complete the survey and indicate interest in joining SharES, a list will be compiled and from that a representative group of 25 surgical practices selected to represent geographic diversity, Spanish-speaking patient populations, and rural-urban variation. Each surgical clinic will receive $1000 as an appreciation of their participation in SharES, paid from the funded grant.

#### Clinicians

Clinician recruitment is concurrent with surgical clinician recruitment, since clinics cannot join the study without at least one committed breast surgeon. Clinicians must agree to utilize the Clinician Dashboard at the time period their practice is randomized to it. Once a surgeon/surgeons at each interested practice is identified, s/he will be rostered with the NCI (if not already), consented and registered. Where possible, participating clinicians will receive a $50 e-gift card for participating.

#### Patients

Eligible patients will be recruited by CRAs and staff at each of the 25 participating surgical clinics. SharES has developed a flexible approach to patient recruitment whereby patients may be recruited before or after their first surgical consult regarding their new diagnosis of breast cancer. This allows the participating clinics and clinicians to determine what works best for their practice; some surgeons prefer to see the patient first and determine whether she is truly eligible to consider surgical treatment options or whether she may need to consider only one option for clinical indication reasons, while other surgeons prefer patients to review patient facing material prior to meeting with them to discuss at the first consult. Patients may be recruited and enrolled in person or remotely using remote consent. Patients will receive a $20 e-gift card following registration and another $20 e-gift card following completion of each follow-up assessment.

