#### Surgical clinics

Eligible clinics will be NCORP-affiliated surgical practices that are rostered and funded components of the NCORP institutions. They are surgical clinics where initial locoregional treatment for breast surgery decision-making is done. Twenty-five surgical clinics will be recruited to participate across NCORP to obtain a representative and diverse cohort of patients. Additional practice eligibility requirements include the following: (1) clinics must annually provide surgical care for over 100 patients newly diagnosed breast cancer patients and (2) clinics must have at least one surgeon who does breast surgery who agrees to participate in the study. These requirements necessitate significant communication between the study team and the clinics to determine which ones have the capacity to participate throughout the study and meet accrual goals. NCORP surgical clinics enrolled in SharES may accept a $1000 incentive following enrollment of the first patient. They may also accept provision of loaner iPads in cases where the patient population may have limited technologic access. Both the incentive and iPads will be charged back to the overall parent grant (R01 CA237046).

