### Who will take informed consent? {26a}

Informed consent will be taken by trained clinical research assistants (CRAs) and/or clinicians at each of the 25 participating surgical clinics. Those taking informed consent have experience doing so from participation in NCORP, for both treatment and CCDR trials. They will take consent from patient and clinician participants, after which participants will be formally enrolled and registered into the Alliance OPEN registration system. Facilitated remote consent is optional.

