## Assignment of intervention: blinding

### Who will be blinded {17a}

The Alliance SDC and CHCR technology team cannot be blinded to the trial arm to which patients are assigned, or to which clinics are randomized, as they are responsible for randomization and allocation. The study investigators (principal investigators and co-investigators) are blinded to the trial arm. Patients will be blinded to which of the iCanDecide websites is the intervention being tested (iCanDecide-ESE) and which is the control (iCanDecide-S). Clinics cannot be blinded because they will be aware roughly 2 weeks prior to when they are allocated to start the Clinician Dashboard to receive training.

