#### Primary outcome analysis

As described, we are testing two interventions, one randomized at the individual level (𝑖) and one at the clinic level (𝑗), rolled out to clinics over six trial time periods (𝑘). The interventions are fully crossed (with intervention and control patients within both intervention and control clinics for every time period). The linear mixed model for the continuous primary outcome (𝑦) patient knowledge has been adapted to a factorial design by adding an individual-level intervention to the model for a hybrid stepped wedge design [32]: 𝑦_𝑖𝑗𝑘_ = 𝛽_0_ + 𝜃_1_𝑥_1𝑖𝑗𝑘_ + 𝜃_2_𝑥_2𝑗𝑘_ + 𝛽_𝑘_𝑡_𝑘_ + 𝑢_𝑗_ + 𝑒_𝑖𝑗𝑘_. Here, 𝑦_𝑖𝑗𝑘_ denotes the response corresponding to individual 𝑖 at time period 𝑘 from clinic 𝑗 (𝑖 = 1, … , 𝑚_𝑗𝑘_ ; 𝑗 = 1, … , 25; 𝑘 = 1, … , 6). The variable 𝑥_1𝑖𝑗𝑘_ (=0, 1) denotes the intervention status of patient 𝑖 enrolled in clinic 𝑗 at time period 𝑘. The variable 𝑥_2𝑗𝑘_ (=0, 1) denotes the intervention status of this patient’s clinic 𝑗 at the 𝑘𝑡ℎ time period. The variable 𝑡_𝑘_ (=0, 1) is the indicator for time period 𝑘 and the term 𝛽_𝑘_ represents the corresponding fixed categorical effect to model the underlying secular trend (𝑘 in 1, …, 5, 𝛽_6_ = 0 for identifiability). The random effect 𝑢_𝑗_ is a random intercept for clinic 𝑗 and represents the time invariant deviation of the 𝑗𝑡ℎ clinic from the population average. The term 𝑒_𝑖𝑗𝑘_ is the patient error term. The term 𝛽_0_ is the intercept. The terms 𝜃_1_ and 𝜃_2_ represent the intervention effect of iCanDecide-ESE and the intervention effect of the Clinician Dashboard, respectively. As one of the most effective ways to improve the statistical power in cluster randomized trials [32, 33], the two patient-level stratification factors (race; education status) as well as an indicator for Hispanic/Latina (yes; no) that are expected to be strongly associated with the outcome knowledge will be included in the model as supportive analysis. The model assumes that an underlying time effect is the same for each clinic. To allow for potential clinic-level fluctuations of the time effect related to the roll out of the Clinician Dashboard, the random effect (𝑢𝑡)_𝑘_ (i.e., a clinic effect interacting with time) will be included in sensitivity analysis. Additionally, sensitivity analyses will account for nesting within clinician.

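### Patients are recruited by clinic staff who know the Dashboard status, with enrolment timing left to the clinic, and the primary model for the Dashboard effect has no patient covariates

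*Protocol article*

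**What the plan says.** Clinic-level randomization (16a) allocates all 25 clinics before activation: five with the Dashboard throughout, five never, and three starting at each of T2 to T6. Section 17a states: "Clinics cannot be blinded because they will be aware roughly 2 weeks prior to when they are allocated to start the Clinician Dashboard".

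Patients come in afterwards, through the clinic. Recruitment (15) has: "Eligible patients will be recruited by CRAs and staff at each of the 25 participating surgical clinics". Section 26a has: "Informed consent will be taken by trained clinical research assistants (CRAs) and/or clinicians at each of the 25 participating surgical clinics". Under the eligibility and intervention sections, participating clinicians are also the Dashboard users.

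On timing, "patients may be recruited before or after their first surgical consult", and "This allows the participating clinics and clinicians to determine what works best for their practice". The reason given is that some surgeons want to see the patient first to "determine whether she is truly eligible to consider surgical treatment options or whether she may need to consider only one option", while others want her to use the material before the visit.

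The primary model in 20a contains the two interventions, period effects and a random clinic intercept. Race, education and Hispanic ethnicity, which the protocol expects to be strongly associated with knowledge, "will be included in the model as supportive analysis".

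**The concern.** The two co-primary comparisons are protected differently. Patients are randomised centrally to an iCanDecide version after enrolment, and patients and clinicians are blinded to it, so who enters the trial cannot depend on the version. Dashboard status is fixed and known before patients are approached, so who enters can depend on it.

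Timing is the concrete route. Enrolment after the consult lets a surgeon filter on whether the patient has a real choice of treatment; enrolment before it does not. The Dashboard fills only after a patient has used iCanDecide, so use before the first visit requires enrolment before that visit. That gives a clinic a plausible reason to move enrolment earlier once the Dashboard is on.

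A change that coincides with activation is confounded with the Dashboard indicator. Period effects common to all clinics cannot separate the two, and a time-invariant clinic intercept cannot either. At stake are a co-primary test and, because both co-primary tests must succeed first, access to the key secondary family.

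**Working it through.** **Inputs from the protocol.** 25 clinics; six 12-week periods; 5 always on, 3 starting at each of T2 to T6, 5 never on (16a); about 4 evaluable patients per clinic-period, target effect 0.35 SD, alpha 0.05 (taken as two-sided), ICC 0.01 to 0.20, at least 700 enrolled (14); clinic volume: "clinics must annually provide surgical care for over 100 patients newly diagnosed breast cancer patients" (Surgical clinics).

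**1. The plan's own power figure.** Generalised least squares on clinic-period means under the 20a model, total SD 1, gives the SE of θ2; power = Φ(0.35/SE − 1.96).

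| ICC | SE(θ2) | Power at 0.35 SD |
|---|---|---|
| 0.01 | 0.0952 | 95.7% |
| 0.05 | 0.1089 | 89.5% |
| 0.15 | 0.1189 | 83.7% |
| 0.20 | 0.1193 | 83.5% |

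The stated power of at least 80% reproduces, so these SEs are a sound base.

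**2. Room for discretion.** At the volume floor, 100 × 12/52 = 23.1 new surgical patients per clinic-period. Enrolment averages 700/(25 × 6) = 4.67. The ratio is 4.67/23.1 = 20.2%. The denominator is all new surgical patients, not eligible ones. If 80% or 50% of them were eligible and under a consented clinician (assumed), the figure would be 25% or 40%; at a volume of 200 a year with all eligible it would be 10%.

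**3. Size of a shift (assumed).** Bias = change in the share of a patient type × its knowledge gap. No document figure exists for either factor. A change of 10 to 30 points and a gap of 0.3 to 0.5 SD include, for example, 0.10 × 0.5 = 0.05, 0.30 × 0.3 = 0.09, 0.20 × 0.5 = 0.10 and 0.30 × 0.5 = 0.15 SD.

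**4. Effect on the test if every Dashboard-on cell shifts by d.** The whole of d then enters θ2, and the false-positive rate is Φ(d/SE − 1.96) + Φ(−d/SE − 1.96). At ICC 0.15 (SE 0.1189):

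| d (SD) | d/SE | False-positive rate |
|---|---|---|
| 0.05 | 0.42 | 7% |
| 0.09 | 0.76 | 12% |
| 0.10 | 0.84 | 13% |
| 0.15 | 1.26 | 24% |

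At ICC 0.01 the last two rows become 18% and 35%, because the SE is smaller.

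**5. If only some clinics shift.** Putting the shift into the same GLS estimator:
- All 15 crossover clinics change at activation and the always-on clinics do not differ: 81% of d reaches θ2 at ICC 0.15, and 56% at ICC 0.01. For d = 0.10 at ICC 0.15 the bias is 0.081 SD, 0.081/0.1189 = 0.68, and the rate is about 10%.
- Only 5 of the 15 change (average over steps): 81%/3 = 27%. For d = 0.10 the bias is 0.027 SD and the rate is 5.6%.
- Only the five always-on clinics differ: the remaining 100% − 81% = 19% at ICC 0.15.

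**6. Constant habits.** A timing preference held throughout by a crossover clinic does not move with activation and goes largely into the clinic intercept. In always-on and never-on clinics there is no within-clinic contrast, so a practice shaped by their status acts through the between-clinic comparison.

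**The case against.** The strongest reply is that the damaging step is not in the text. The timing rule reads as an accommodation of each practice, not as licence to vary timing with Dashboard status, and the Dashboard is described as usable before or after the first visit, so activation forces no change. A stable habit does little harm. The shift sizes are assumed, and nothing in the document links timing or having one option to knowledge, or gives a direction. All of this stands, and it limits the point to a risk of unknown size.

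Four stronger readings are tempting and are not supported:
- *Staff hand-pick one in five eligible patients.* The 20% uses all new surgical patients at the volume floor. The eligible share is not given, refusals also lower it, and the enrolment target is a planning average, not a per-period cap.
- *Error is inflated to 24%.* That needs the largest assumed shift in every Dashboard-on cell; step 5 shows how quickly it falls.
- *No screening log or approach order exists.* A journal article commonly leaves these to the full protocol, which is not shown. The point does not rest on them.
- *Enrolment timing belongs in the primary model.* On this very argument Dashboard status may affect timing, so adjusting the primary estimate for it is contestable.

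It is also fair that race, education and ethnicity are not the same thing as having one option or several. Adjusting for them removes only part of any imbalance.

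What the reply does not remove are the stated facts: allocation first, status known, recruitment and consent by the same clinics, timing at their discretion, and a primary model without patient covariates. The inverse probability weighting in 20c addresses survey non-response, not who is enrolled.

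**Conclusion.** The concern holds as a design vulnerability of the Dashboard comparison, not as a demonstrated bias. θ2 is biased if recruitment or timing changes at activation, or differs because of status between always-on and never-on clinics, in a way related to knowledge. The protocol supplies the conditions for this but does not say it will happen.

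The illustration is about 7% to 24% false positives at ICC 0.15 for shifts of 0.05 to 0.15 SD, which are 14% to 43% of the 0.35 SD target (0.05/0.35 and 0.15/0.35). It rests on assumed shifts, on every Dashboard-on cell moving equally, and on the Dashboard test being reached in the fixed sequence. With partial change the inflation can be small. θ1 is unaffected. The change is worth making because it is cheap and the Dashboard result has no other protection in the stated primary analysis.

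**What to change.** **(a) In 20a,** make the model adjusted for race, education and Hispanic ethnicity the primary model, and keep the unadjusted model as supportive. Race and education are already allocation factors, and the protocol itself presents such adjustment as a gain in power. It removes imbalance on these factors, not on unmeasured ones. It needs no new data, only a change in the order of two planned models.

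**(b) In Recruitment (15),** have each clinic, or each participating surgeon where practice differs within a clinic, declare before learning its step whether it enrols before or after the first consult, and keep that choice in all six periods. Record the enrolment date relative to the first consult. Report case mix and timing by Dashboard status, and use timing only in a sensitivity analysis.

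The cost is some loss of flexibility in timing for surgeons and one extra recorded date. The sample size does not change.

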## Assignment of interventions: allocation/randomization

### Sequence generation {16a}

Both clinics and patients will be randomized; cluster randomization for clinics in a hybrid stepped wedge fashion and individual randomization for patients is described below.

#### Clinic-level randomization

Twenty-five clinics will be identified for participation. Prior to study activation, clinics will be randomized to their respective time period (or “step”). Five clinics will be randomly allocated to receive the Clinician Dashboard for the entire duration of the study and five clinics will be randomly allocated to control with no Clinician Dashboard. Groups of three clinics will be randomly allocated to one of the five steps that have the Clinician Dashboard activated at a later time period (i.e., T2, T3, T4, T5, T6) (Fig. 2). Clinic-level randomization will not be stratified.

